## Communicating results to patients

In accordance with Article L1122-1 of the French Public Health Code, patients will be informed of the overall results of the study during an oral presentation in the various military units.

## Data handover

Data collection and management is the responsibility of the IRBA. Conditions for the handover of all or part of the study’s database will be decided by the Direction centrale du Service de santé des armées (the sponsor) and will be the subject of a written contract.

Appendix 1 : Summary of studies evaluating the effects of POT.

| **Population** | **Performance / Target** | **Results / Limitations** | **Reference** (if available) | **POT Program** |
| --- | --- | --- | --- | --- |
| Students in 1st year of medicine (officer cadet) and business school | Cognitive performances | Benefits of POT. on feeling of efficiency in preparation for a competitive examination/exam  Limitations: absence of control | (Steiler D., 2011) | 8 weeks  1h/week + daily practice exercises |
| Air force pilots | Cognitive performance | Benefit of T.O.P. on ejection decision making in simulator  Limit: 5 subjects | (Millet, 2013) | Memory not searchable |
| 16th BC on Sentinel mission | Psycho-cognitive and physical performance, stress level | Project PHYTOP  Benefits on cognitive performance (memory test) and improvement in stress tolerance resources (optimism and motivation) | Non publié | Unpublished Training 1h30 weekly combined with 1h30 supervised sports practice - 9 weeks |
| Paris Fire Brigade | Stress management | Effectiveness of techniques on perceived stress, negative mood, local immunity and post-traumatic stress measurement.  Cardiac Coherence (CC) seems to be more effective on immunity, while POT is more effective in reducing perceived stress.  Single-center randomized study | (Trousselard, Fidier, Ferhani, & Perraut-Pierre, 2010) | Regular training for 2 months |
| Submariners in operational situations on nuclear-powered submarines | Stress management / Sleep management  Association POT and CC | Benefits of POT for both on-watch and off-watch submariners.  Mixed evaluation: subjective for mood disorders and objective for sleep measurement in operational conditions | (Crosnier, 2013) | Dissertation not available |
| Air Force pilots on OPEX | Operational performance and perceived stress on mission | Afghanistan Decrease in perceived stress, feelings of fatigue, urinary cortisol excretion, as well as improved group cohesion, particularly in squadron leader cohesion (vertical cohesion) for the two squadrons that benefited from these techniques.  Randomized study | (Trousselard M., 2010) | 8 weeks  1h/week + practice exercises between 2 sessions |
| Infantry soldiers | Operational performance | Benefits of short, intense TOP training (two hours daily) on motor performance (rope climbing) and technical performance (FAMAS assembly and disassembly) | (Dirand, 2014) | 2 hours daily - over a short period |

Appendix 2: Details of the programs’ contents

**Sessions - Active Control Group**

| **Session number** | **Main idea** | **Cognitive process** | **Activity/ activities** | **Organization of the session**  **(duration, group)** |
| --- | --- | --- | --- | --- |
| 1 | Presentation and identification of the different sensory channels | Perception and attention | Presentation of VAKOG  (Visual, Auditory, Olfactory and Gustatory)  Identification of the main sensory channel  Example applications | 45–60 minutes  In groups of 20/25 people maximum  Practical exercises in groups of 5 to 10 participants, depending on the activity |
|  | Integration of information | Memory /  Working memory | Presentation of memory processes, with a focus on working memory  Example of an optimization tool: the Memory Palace  Practical exercises working in pairs and groups |  |
| 3 | Reasoning 1 | Reasoning, coping strategy | Presentation of the different types of reasoning  Individual and group ‘psycho-technical’-type exercises |  |
| 4 | Reasoning 2 | Conceptualization, expression and communication of ideas | Dissertation topics: immortality, new technologies in the military, self-sacrifice, emotions and taking action, etc. |  |
| 5 | Mental procedure before taking action | Mental imaging | Presentation of mental imagery, its use in the professional context and performance objectives (example of the PAF and high-level athletes)  Individual exercises (the tower of Hanoi), then as a group (the marshmallow challenge) |  |
| 6 | Faced with a problem, using imagination and creativity as a solution | Imagination, divergent and convergent thinking | Presentation of the theme ‘creativity and active thinking’  Individual problem-solving exercises and inter-group challenges |  |

* Divergent thinking: producing many ideas from one stimulus. Convergent thinking: producing a single solution that integrates several elements.

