### The intervention

The POTs intervention will consist of practical courses run by the designated POTs instructor in each military unit. This person is a member of the military who has completed the POT trainer course delivered by the French Centre National des Sports de Défense. The intervention is divided into six, one-hour sessions, spread over three weeks, with two sessions per week. The first two sessions will be scheduled at the start of the selection course (ideally the day before it begins).

The intervention will include theoretical instruction and practical exercises in POTs that have been identified as useful in increasing body awareness (paying attention to breathing, muscle relaxation, mental imagery). The contents of the six sessions will be established and validated beforehand by POTs instructors from the six military units, under the supervision of the POTs instructor who coordinates the intervention.

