### The active control

The active control will unfold in the same way as the POTs intervention: there will be six one-hour sessions, spread over the three weeks of the study, with two sessions per week. These sessions will consist of exercises (details of the sessions are available in APPENDIX 2 ) that focus on high-level cognitive processes such as reasoning, information processing and creativity. They will be divided into two p3arts: the first, theoretical component will describe the processes that will be the focus of the session, and the second, practical component will focus on exercises.

These sessions will be carried out under the supervision of the person responsible for the POTs intervention that will take place the following year (the POTs instructor).

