## Exclusion criteria

- Participants who have already completed an ‘advanced’ POTs training program (> 10 hours)^[[3]](#footnote-3)^
- Refusal to participate
- Person covered by articles L1121-5 to L1121-8 of the public health code, as follows:
  - A pregnant^[[4]](#footnote-4)^, parturient or nursing woman,
  - A person detained following a judicial or administrative decision,
  - Persons who are subject to psychiatric monitoring under articles L3112-1 and L3113-1, and who are not covered by the provisions of article L1121-8,
  - Adults made a ward of court, or who are unable to give their consent.

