# STATISTICAL ASPECTS

## Calculating the number of subjects required

To date, there are no data in the literature on the effectiveness of POTs in preventing sports-related injuries. However, discussions with military unit managers and medical officers suggest that a reduction in the injury rate of around 15% would be clinically relevant. Preliminary epidemiological data from the various units indicates that the rate of fall injuries is around 50%.

To determine the sample size required to observe a significant difference in rates between the two groups, we used the following parameters:

- statistical test: two-tailed
- fall rate in the active control group: 50%
- fall rate in the POTs group: 35%
- statistical significance = 0.05
- power = 0.80

Taking into account potential drop-outs (estimated at 10%), the sample should consist of 200 participants per group, for a total of 400 participants over the two years of the study.

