**Sessions - ORAF Group**

| **Session number** | **Theme** | **Techniques worked on** | **Content** | **Organization of the session**  **(duration, group)** |
| --- | --- | --- | --- | --- |
| 1 | ORAF Presentation - Breathing | Breathing - Relaxation | Presentation of the ORAF: philosophy, theory & application  Breathing: theory and practice | 45 to 60 minutes  In groups of up to 20 people |
| 2 | Sleep and Vigilance | Relaxing breathing and calm imagery | Sleep/Vigilance/Fatigue theory  Continual awareness of the whole body through relaxation (recovery and relaxation); using VAKOG to support an internal dialogue/relaxing imagery |  |
| 3 | Stress | The optimized activation signal (OAS) technique | Theoretical presentation of stress  Implementation of the OAS technique |  |
| 4 | Self-confidence, performance optimization | Relaxing breathing  Mental rehearsal | Mental rehearsal: presentation and practical exercise |  |
| 5 | Mindfulness and performance optimization | Geolocation  (taking the environment into account)  Dynamic breathing | Practical geolocation exercise, optimized complete dynamization and immediate mental projection |  |
| 6 | Motivation and performance | Relaxation  Mental projection of goals (MPG) | Motivation theory + MPG  Individual relaxation exercise, followed by an MPG exercise |  |

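### Control session 5 presents mental imagery, a named POTs technique, and prior POTs hours are not among the listed clinical data, so the contrast may be narrowed or confounded by an unknown, probably small, amount

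*Protocol*

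**What the plan says.** **Active content.** Protocol, The intervention, describes six one-hour sessions, two per week over three weeks, built on techniques "identified as useful in increasing body awareness (paying attention to breathing, muscle relaxation, mental imagery"). Raising body awareness is the hypothesised route to fewer falls.

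**Control content.** Protocol, The active control, describes a matching schedule of exercises that "focus on high-level cognitive processes such as reasoning, information processing and creativity" and refers to Appendix 2 for detail. There, session 5 has mental imaging as its cognitive process and opens with "Presentation of mental imagery, its use in the professional context and performance objectives", using high-level athletes as one example. Its exercises are the Tower of Hanoi and the marshmallow challenge.

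**Contamination.** Protocol, Randomization, rejects individual allocation because POTs participants could influence controls. All units therefore run the control in year Y and POTs in year Y+1.

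**Prior POTs.** Exclusion criteria remove only those with an advanced "POTs training program (> 10 hours"). The footnote ties that limit to the Ministry's 10-hour initial training, so someone who has completed all of it remains eligible in either group. Clinical parameters limits clinical data to injury history, age, sex, height and weight. Analysis of the main objective uses a Cox model with unspecified clinical variables as potential confounders.

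**The concern.** There are two separate issues.

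First, the protocol accepts a non-randomised comparison of successive years as the price of keeping POTs content from controls, and then writes one named POTs technique into the control programme. If imagery works as the protocol supposes, any benefit to controls lowers the control rate and shrinks the difference the trial is sized to detect.

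Second, eligible candidates may already have had more POTs (up to 10 hours) than the trial gives (6 hours). Such exposure is plausible: Current knowledge says POTs are being deployed across the armed forces, and the Paris Fire Brigade, a participating unit, appears in Appendix 1 as an earlier POTs study population. Because group and calendar year coincide, a programme that is still spreading could leave the two years with different amounts of prior training. That would confound the comparison, in a direction that cannot be known in advance. If exposure is equal in both years, it can still attenuate the effect. Neither can be examined if prior hours are not recorded.

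**Working it through.** **1. The plan's own sample size.** Inputs from Calculating the number of subjects required: "statistical test: two-tailed"; "fall rate in the active control group: 50" per cent; "fall rate in the POTs group: 35" per cent; alpha 0.05; power 0.80; drop-out 10%; 200 per group.

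Pooled formula: n = [1.96·√(2·0.425·0.575) + 0.842·√(0.50·0.50 + 0.35·0.65)]² / 0.15² = [1.96·0.6991 + 0.842·0.6910]² / 0.0225, giving 170 per group. With the continuity correction, n = 183. After drop-out, 183/0.9 gives 204 and 183·1.1 gives 202; without the correction, 170/0.9 gives 189. The stated 200 is reproduced, so the sample size is not miscalculated.

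Evaluable per group: 200·0.9 = 180. Power = Φ[(0.15·√180 − 1.96·0.6991)/0.6910] = Φ(0.929) = 82%.

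**2. When session 5 can act.** With two sessions per week over three weeks, session 5 falls in week 3. End-of-study visit closes follow-up the day after the last session. Falls in weeks 1 and 2 cannot be affected, so at most about the last third of follow-up is exposed.

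**3. Illustration.** Assumptions not in the documents: constant hazard, the POTs rate held at 35%, and session 5 giving controls one sixth of the POTs effect on the log hazard during the last third only.

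- Planned hazard ratio: ln(0.65)/ln(0.50) = 0.621.
- One sixth of the effect: 0.621^(1/6) = 0.924.
- Control cumulative hazard: 0.6931·(2/3 + 0.924/3) = 0.6755.
- Control rate: 1 − exp(−0.6755) = 49.1%, a difference of 14.1 points.
- Power: Φ[(0.1411·√180 − 1.96·0.6981)/0.6910] = Φ(0.760) = 78%.

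**4. Range.** With half of that assumed effect, the ratio is 0.621^(1/12) = 0.961, the control rate is 1 − exp[−0.6931·(2/3 + 0.961/3)] = 49.5%, and power is about 80%.

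| Assumed session-5 effect, last third only | Control rate | Power, 180 per group |
|---|---|---|
| None | 50.0% | 82% |
| One twelfth of the POTs effect | 49.5% | 80% |
| One sixth of the POTs effect | 49.1% | 78% |

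**5. Prior POTs.** No power figure is offered. The documents give neither the share of candidates with prior training nor how long its effect lasts; persistence is itself the fourth secondary objective. The 50% rate comes from unit data that may already include trained people, so lowering it again for prior training could count the same exposure twice.

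**The case against.** The strongest reply is that one presentation is not a dose of the programme. The exercises in control session 5 are problem-solving tasks, whereas the POTs group practises imagery, rehearsal or mental projection in several sessions alongside breathing and relaxation. This stands, and it is why even one sixth is generous. A reader might spread that one sixth over the whole of follow-up and infer a much larger loss of power; the session's timing rules that out.

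A reader might also infer three further faults that the documents do not support.

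- **VAKOG.** It appears in control session 1 and again in the POTs group, "using VAKOG to support an internal dialogue/relaxing imagery". It is not among the techniques named in The intervention; controls identify sensory channels, while the POTs group uses it as an aid to relaxation.
- **The POTs instructor supervising control sessions.** This holds instructor and attention constant across groups, and no harm from it is shown.
- **A null result being uninterpretable.** Attenuation would make a positive result conservative, and postural awareness is measured before each session in both groups, so the data can show whether control sessions moved the presumed mechanism.

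Nor does The active control strictly contradict Appendix 2: its list of processes is only illustrative.

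On prior POTs, the 10-hour limit is a defined eligibility choice, applied equally to both groups and consistent with a programme already in use. It is not an error, and not by itself a directional bias. Prior POTs must be ascertained for screening, the items of the medico-demographic questionnaire are not shown, and the Cox covariates may be listed in a statistical analysis plan. What remains is that the protocol does not say hours below the limit will be recorded, and an analysis plan cannot adjust for a variable that was not collected.

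**Conclusion.** The point holds as two modest weaknesses that are cheap to remove. A named POTs technique is presented in control session 5, in a design that gave up individual randomisation to avoid such contamination. On the protocol's premise that imagery raises body awareness and so lowers fall risk, this can only narrow the contrast. The size is not derivable and is probably small: the assumed one-sixth effect in the last third of follow-up costs about 5 points of power (82% to 78%), which takes it just below the planned 80%. That rests on constant hazard, an unchanged 35% rate with POTs and 180 evaluable per group.

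Separately, prior POTs of up to 10 hours is admitted in both groups and is absent from the listed clinical data. In a comparison of successive years it may attenuate the effect or, if it differs between years, confound it. Neither size nor direction can be given. The sample-size arithmetic and the eligibility rule are not at fault.

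**What to change.** Before year Y:

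- Replace the mental imagery content of control session 5 with content that is not a named POTs technique, so that The intervention, The active control and Appendix 2 agree.
- Keep the eligibility rule. Record hours of prior POTs as an item in the existing medico-demographic questionnaire, in both years.
- Include prior hours as a covariate in the primary Cox model.
- Add a sensitivity analysis restricted to participants with no prior POTs in both groups.

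The cost is minor rework of one session by the instructors, one questionnaire item and one covariate. The restricted analysis will have fewer participants, by a number the documents do not give, so it should be read as supportive. Adjustment deals only with measured prior training; other differences between the two years remain.

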**Sessions - ORAF Group**

| **Session number** | **Theme** | **Techniques worked on** | **Content** | **Organization of the session**  **(duration, group)** |
| --- | --- | --- | --- | --- |
| 1 | ORAF Presentation - Breathing | Breathing - Relaxation | Presentation of the ORAF: philosophy, theory & application  Breathing: theory and practice | 45 to 60 minutes  In groups of up to 20 people |
| 2 | Sleep and Vigilance | Relaxing breathing and calm imagery | Sleep/Vigilance/Fatigue theory  Continual awareness of the whole body through relaxation (recovery and relaxation); using VAKOG to support an internal dialogue/relaxing imagery |  |
| 3 | Stress | The optimized activation signal (OAS) technique | Theoretical presentation of stress  Implementation of the OAS technique |  |
| 4 | Self-confidence, performance optimization | Relaxing breathing  Mental rehearsal | Mental rehearsal: presentation and practical exercise |  |
| 5 | Mindfulness and performance optimization | Geolocation  (taking the environment into account)  Dynamic breathing | Practical geolocation exercise, optimized complete dynamization and immediate mental projection |  |
| 6 | Motivation and performance | Relaxation  Mental projection of goals (MPG) | Motivation theory + MPG  Individual relaxation exercise, followed by an MPG exercise |  |

Appendix 3 : PAS and PSS questionnaires

| **Questionnaire PAS** | | 1  Ne me correspond pas du tout | 2 | 3 | 4  Me correspond moyennement | 5 | 6 | 7  Me correspond fortement |
| --- | --- | --- | --- | --- | --- | --- | --- | --- |
| 1 | J'ai besoin d'être très concentré(e) pour prendre conscience de ma posture corporelle |  |  |  |  |  |  |  |
| 2 | Quand je me tiens dans une mauvaise posture corporelle, souvent je ne la remarque pas avant qu'elle devienne douloureuse |  |  |  |  |  |  |  |
| 3 | Quand je suis assis(e), j’ai souvent tendance à m’avachir |  |  |  |  |  |  |  |
| 4 | Quand je me concentre sur une activité spécifique, je prends souvent une posture corporelle particulière sans m'en rendre compte |  |  |  |  |  |  |  |
| 5 | Quand je me concentre sur une activité spécifique, je prends souvent une posture corporelle particulière sans m'en rendre compte |  |  |  |  |  |  |  |
| 6 | Quand je me concentre sur une activité spécifique, je prends souvent une posture corporelle particulière sans m'en rendre compte |  |  |  |  |  |  |  |
| 7 | Au travers de ma posture corporelle, je peux intentionnellement modifier l'impression que je donne aux autres |  |  |  |  |  |  |  |
| 8 | Tout au long de la journée, je suis en permanence conscient(e) de la façon dont je suis assis(e) ou debout |  |  |  |  |  |  |  |
| 9 | Je suis souvent conscient(e) / me rends compte de ma posture corporelle du moment, que je sois assis(e) ou debout |  |  |  |  |  |  |  |
| 10 | Même si je suis focalisé(e) sur quelque chose, je suis en permanence conscient(e) de ma posture corporelle |  |  |  |  |  |  |  |
| 11 | Au travers de ma posture corporelle, je peux contrôler consciemment mon humeur |  |  |  |  |  |  |  |
| 12 | Je remarque si ma posture corporelle est bonne pour moi, ou non, seulement quand je me concentre dessus |  |  |  |  |  |  |  |

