## Secondary endpoints

Criteria for meeting the study’s four secondary objectives are as follows:

- - 1. The first secondary objective comprises two evaluation criteria: 1) self-reported scores on the Postural Awareness Scale (APPENDIX 3) pre- and post-intervention, and at the start of each session; 2) variation in measures of postural balance pre- and post-intervention.
    2. The second objective also comprises two criteria: 1) self-reported scores on Cohen’s Perceived Stress questionnaire (APPENDIX 3) pre- and post-intervention, and at the start of each session; 2) variation in measures of allostatic load in saliva pre- and post-intervention (the corticotropic axis: cortisol, DHEA, oxidative stress; the autonomic nervous system: alpha amylase and chromogranin A).
    3. The evaluation criterion for the third secondary objective will be the correct prediction of the risk of fall injury by the machine learning model.
    4. The evaluation criterion for the fourth secondary objective will be the rate of fall injuries in each of the two groups (POTs *vs.* active control), in the period between the end of the study and the end of the selection course. Information about when each participant left the course will be collected from the physician responsible.

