### Para-clinical parameters

Postural balance will be measured by a clinical test (the BESS) and posturography.

1. The Balance Error Scoring System (BESS)

The BESS assesses static postural balance (eyes closed) in six conditions, using three positions (double leg stance *vs.* single leg stance *vs.* tandem stance) on two surfaces (firm *vs.* soft) (Figure 5). The participant must remain balanced without moving for 20 seconds. Points are given for postural errors (e.g., eye opening, hip flexion greater than 30°, etc.). The sum of the points obtained in the six conditions gives the total BESS score (Docherty et al., 2006)

 
[figure not shown]

**Figure 5 –** The Balance Error Scoring System is a clinical test that assesses static postural balance in six conditions, using three positions (double leg stance *vs.* single leg stance *vs.* tandem stance) on two surfaces (firm *vs.* soft).

1. Posturography

Posturography is the recording of static postural balance using a stabilometric platform (FEETEST 6^©^, Techno Concept^®^, France) (Figure 6). It consists of four small platforms that locate the position of the body’s center of pressure from the coordinates of four points of contact (left heel, left metatarsal, right heel and right metatarsal). Postural recording takes place with eyes closed, and lasts approximately one.

[figure not shown]

**Figure 6** – The FEETEST 6^©^ platform (Techno Concept^®^).

To ensure reproducibility in measurements of para-clinical parameters, investigators from the units involved in the initial assessment visit will be trained in how to carry out the BESS test (using a video). Similarly, a standard procedure will be put in place for posturography measurements.

1. Psychometric data

Self-report questionnaires will be used to measure postural awareness (the Postural Awareness Scale) and perceived stress (Cohen’s Perceived Stress Scale).

- 1. The Postural Awareness Scale (Cramer, Mehling, Saha, Dobos, & Lauche, 2018)

This questionnaire evaluates body awareness involved in postural control. A French version is currently being validated. The questionnaire is made up of 12 items, each rated from 1 (not at all true about me) to 7 (very true about me). The questionnaire assesses two dimensions of postural awareness: (*i*) Ease/Familiarity with Postural Awareness; and (*ii*) Need for Attention Regulation with Postural Awareness.

- 1. Cohen’s Perceived Stress Scale (Cohen, Kamarck, & Mermelstein, 1983)

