This questionnaire evaluates how individuals rate their perception of stress. It consists of 14 items, each rated from 1 (never) to 5 (often). A high score on the questionnaire indicates a high level of perceived stress.

The two questionnaires are presented in APPENDIX 3. Participants will complete paper-based versions.

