**Analysis of secondary objectives**

For the first secondary objective, the effect of the POTs intervention on postural awareness will be evaluated by comparing the following for the POTs group: (*i*) scores on the Postural Awareness Scale at the six measurement times (repeated measures ANOVA), and (*ii*) posturography measurements pre- and post-intervention (paired samples comparison of means).

For the second secondary objective, the effect of the POTs intervention on the psychobiological stress response will be evaluated by comparing the following measures for the POTs group at all six measurement times: (*i*) scores on Cohen’s Perceived Stress Questionnaire (repeated measures ANOVA), and (*ii*) biological stress variables (paired samples comparison of means).

For the third secondary objective, machine learning will be used to evaluate the accuracy of the predictive model of the risk of fall injury using the following calculation:

|  | $\text{Accuracy=}\frac{\text{True }\text{Fall-related injury }\text{participants + True }\text{Non-fall }\text{participants}}{\text{Total number of participants}}$ |  |
| --- | --- | --- |

where N_prediction of trauma_ is the number of participants for whom the machine learning model predicts the occurrence of a fall injury and who do, in fact, suffer a fall injury during the selection course; N_prediction of_ _good health_ is the number of participants for whom the model predicts the non-occurrence of a fall injury and who do not, in fact, suffer a fall injury during the selection course; and N_total_ is the total number of participants included in the study.

For the fourth secondary objective, the long-term effectiveness of the POTs intervention in preventing fall injuries between the end of the study and the end of the selection course will be evaluated using a comparative survival analysis (the Cox model). Survival curves for POTs and active control groups will be compared using the log-rank test.

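### The Postural Awareness Scale in Appendix 3 prints one sentence in rows 4, 5 and 6, so it holds 10 distinct items instead of the stated 12

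*Protocol*

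**What the plan says.** Under Para-clinical parameters, the protocol says of the Postural Awareness Scale: "The questionnaire is made up of 12 items". Each item is rated from 1 to 7. It adds "The questionnaire assesses two dimensions of postural awareness", without saying which items belong to which dimension, and "A French version is currently being validated". The same section closes its account of the psychometric data with "The two questionnaires are presented in APPENDIX 3. Participants will complete paper-based versions".

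Secondary endpoints makes the scale the first of two criteria for the first secondary objective: "self-reported scores on the Postural Awareness Scale (APPENDIX 3) pre- and post-intervention, and at the start of each session". The other criterion is the change in postural balance measures. Analysis of secondary objectives then plans to compare, within the POTs group, "scores on the Postural Awareness Scale at the six measurement times (repeated measures ANOVA").

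In Appendix 3 the scale is a table of 12 numbered rows. Rows 4, 5 and 6 all begin "Quand je me concentre sur une activité spécifique, je prends souvent une posture corporelle particulière" and continue identically to the last word.

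**The concern.** The body of the protocol promises 12 items and the appendix delivers 10. The appendix is not background material: the endpoint definition cites it, and the description of the questionnaires points to it for the instrument that participants fill in on paper. Someone preparing the forms from this protocol would reproduce the error.

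A score from such a form would not be the 12-item scale. One statement would be weighted three times, the content of two items would be lost, and three answers to the same sentence would tend to raise an internal-consistency coefficient without adding information. The scale is the only self-report measure of postural awareness, the mechanism through which the programme is hypothesised to work. Item content not collected at a visit cannot be recovered later.

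**Working it through.** **Inputs**

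- Stated number of items: 12, each rated 1 to 7 (Para-clinical parameters).
- Printed items: the 12 numbered rows of the table in Appendix 3.
- Scoring rule: none is given, so an unweighted sum is assumed below.

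**Count of items**

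The row texts were compared as exact strings. One sentence occurs three times (rows 4, 5 and 6) and nine sentences occur once.

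- Numbered rows: 3 + 9 = 12. This matches the stated figure.
- Distinct items: 1 + 9 = 10. This does not.
- Items missing: 12 − 10 = 2.

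**Weight of the repeated sentence in an unweighted total**

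- As intended: 1/12 = 8.3%.
- As printed: 3/12 = 25%.

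The score range gives the same share. The total runs from 12 × 1 = 12 to 12 × 7 = 84, a span of 72. Three copies of one sentence span 3 × (7 − 1) = 18, and 18/72 = 25%.

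**Would routine checks reveal it?**

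Not a range check. The form still has 12 rows, so the nominal range stays 12 to 84, the same as for a correct form.

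**Effect on the two dimensions**

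This cannot be computed, because the protocol does not allocate items to dimensions.

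**Could it be a text-extraction artefact?**

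This is unlikely. Each of the three rows has its own number and its full text. Where cells are merged elsewhere, as in the last column of the session tables in Appendix 2, they come out blank and are not repeated.

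**What depends on the scale**

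| Element | Uses the scale? |
| --- | --- |
| Primary endpoint (fall injuries) | No |
| First secondary objective, questionnaire criterion | Yes |
| First secondary objective, posturography criterion | No |
| Second secondary objective (perceived stress, saliva) | No |
| Third secondary objective (prediction from BESS and posturography) | No |
| Fourth secondary objective (later fall injuries) | No |

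**The case against.** The strongest objection is that this may be only a copying slip in the protocol. The text says that the questionnaires are shown in Appendix 3 and completed on paper. It does not say that the appendix page is the field form. Data collection methods says that a paper Case Report Form will be created, and Data flow says that questionnaires are entered by optical reading, which suggests separately laid-out forms. A footnote explaining the programme's name at the time of submission also shows that the text was edited afterwards. This objection stands as a limit: a reader might infer that participants answered one item three times, but the documents do not establish it. It does not remove the contradiction between the appendix and the stated 12 items.

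Three further inferences are tempting and should not be drawn.

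- **Bias between arms.** The control programme runs in year Y and POTs in year Y+1, so a form corrected between years would coincide with the change of arm. The planned test of the scale, however, is within the POTs group only, all enrolled in year Y+1. A correction between years would affect only descriptive summaries by group or an unplanned comparison, and nothing in the protocol suggests that such a correction is intended.
- **Half of one sub-scale.** That would need six items per dimension and all three repeats in the same one. The documents support neither assumption.
- **Row 4 is right and rows 5 and 6 are wrong.** Nothing shows which of the three positions belongs to the repeated sentence.

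It is also fair to say that the problem is clerical in origin and touches one of two criteria for one of four secondary objectives.

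**Conclusion.** The point holds as an internal contradiction with a conditional consequence. The scale in Appendix 3 has 10 distinct items where the protocol states 12; that follows from a direct count and needs no assumption.

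The consequence for the score rests on two assumptions: that the form is administered as printed, and that the total is unweighted. The repeated sentence then carries 25% of the total in place of 8.3%, and two items are not measured. The planned repeated measures ANOVA in the POTs group would analyse that altered score. Because the protocol describes the French version as still under validation, it does not point to an already validated French form that would guard against the error.

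The correction is worth making because it is nearly free before use, whereas missing items cannot be recovered afterwards.

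**What to change.** 1. Check rows 4 to 6 of Appendix 3 against the source French version and restore the two missing items. The wording and the order must come from that source, since the protocol contains neither.
2. Confirm which form participants actually receive or received. If the field form already has the 12 correct items, only the appendix needs correcting and the data are unaffected.
3. Use the same form in both years, so that scores in the two groups can be described on one instrument.
4. If forms were already completed as printed, count the repeated sentence once, with the rule for combining its three answers fixed in advance. Report the result as a shortened 10-item scale (unweighted range 10 to 70) and do not present it as the 12-item score. Any sub-scale score would first need the item allocation from the source instrument.

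Before use, the cost is one corrected page and one check of the field form. After use, the cost is a shortened score that lacks the content of two items.
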